### Study procedures

#### Recruitment of participants

Individuals to whom THN has been supplied will be screened for eligibility for the study. If eligible, they will be provided with information about the study and asked whether they are willing to participate. Additional consent will be sought from participants who use drugs (groups a. and b.) to use their personal data for linkage to the national/regional death registers to identify any deaths during the study period. Consenting participants will be required to send a text message to the study’s automated telephone system, containing their unique study number (PIN) and initials to be formally enrolled into the study. These data will be captured on the system with a date stamp. They will receive a message by return, welcoming them to the study and this prompts the system to send monthly reminder texts to their mobile.

Staff at recruitment sites can recruit participants face to face or remotely by telephone.

##### Enrolment

All consenting participants will be asked to complete a baseline/enrolment questionnaire with the member of staff recruiting them into the study. The questionnaire will elicit baseline information on sociodemographic characteristics, previous drug use, previous experience of witnessed or experienced overdoses, naloxone provision and training. Participants will be reimbursed for their time with a £5 shopping voucher. In addition, the staff member will complete a brief record of the naloxone and training provided to the participant at the time of recruitment to the study.

#### Follow-up assessments

##### Total cohort

Participants will be sent monthly text message reminders over the 6-month study period to prompt them to contact research staff if they have witnessed an opioid overdose and take part in a witnessed overdose interview. By interviewing participants as soon as possible after they have witnessed an overdose, we hope to reduce any recall issues. Staff who have frequent or regular contact with participants (including instances of replenishment of naloxone supply) will also prompt participants to contact research staff to notify them of any witnessed opioid overdose.

All participants will be contacted by telephone at six months by the research staff and invited to take part in a structured follow-up interview. The interview ascertains if the participant has witnessed an overdose since enrolment (or since contacting the research staff if relevant), actions and outcomes relating to the overdose and use of THN, carriage of THN, and elements relating to their overdose prevention/THN training. All participants who complete this interview will be reimbursed with a £15 shopping voucher.

To reduce loss to follow-up, we will collect contact details from participants at enrolment and provide participants with a modest monetary reimbursement for undertaking the structured interview at six months and the witnessed overdose interview.

##### Witnessed overdose cohort

If the participant reports that they have witnessed an overdose, they will be contacted by research staff and asked to complete a structured questionnaire administered by the researcher either face to face or over the telephone. This questionnaire covers details relating to the overdose event and use of THN, THN carriage, and elements relating to their overdose prevention/THN training. Participants will be reimbursed with a £15 shopping voucher for their time.

##### Sub-study A

The aim of sub-study A is to better understand the effectiveness of the concentrated naloxone nasal-spray educational and training materials delivered to participants. Sub-study A comprises two structured surveys, embedded in i) the Training Form undertaken at Baseline/Enrolment, and ii) the structured questionnaire administered to those participants who report they have witnessed an opioid overdose. Survey one examines training and materials provided and Survey two asks participants about the extent to which they followed the instructions (or equivalent).

##### Sub-study B

The aim of sub-study B is to better understand the use, safety, and effectiveness of different naloxone products. Sub-study B comprises interviews with 60 UK participants from the witnessed overdose cohort. Between 20–40 of these 60 participants will have been provided with concentrated naloxone nasal-spray, while the remainder will have been provided with pre-filled syringes of injectable naloxone.

Qualitative interviews will be conducted by telephone, by a trained researcher. Each interview will be led by a topic guide, last approximately one hour, and be audio recorded. The topic guide has been developed by the authors JN and SP (see Supplementary information: Topic guide). The topic guide will briefly cover the participant’s personal circumstances, current substance use, and treatment situation. It will then capture details of any overdoses experienced or witnessed since the study started before focusing in more depth on the most recent overdose witnessed (circumstances of the opioid overdose, opioid overdose onset, response to the opioid overdose, naloxone administration, impact of the social and environmental setting on naloxone carriage rate and use, effectiveness of naloxone, outcome of the opioid overdose, and longer-term impact of the opioid overdose on the participant). Participants will also be asked about any training they have had, or need, in naloxone administration.

In addition, after the interview, an independent clinical adviser/consultant will review the information and assess the accuracy of the participant’s identification and response to the opioid overdose (as detailed in the transcribed interviews) using a pre-designed 5-point Likert Scale.

#### Mortality data

In addition, the national/regional death registers will be probed to confirm mortality data for study participants who are at risk of experiencing an opioid overdose themselves. Death records will be checked for opioid overdose as cause of death, including toxicology information where available.

#### Safety

Serious and non-serious adverse drug reactions (SADR and ADR) suspected to have a causal relationship with the administration of take-home naloxone will be captured.

Collecting and monitoring safety data in this study is challenging. We are examining the administration of naloxone for overdose reversal, by community members, in a real world setting. Given the nature of this study, serious adverse drug reactions (SADRs) and adverse drug reactions (ADRs) observed by the study participant witnessing the overdose will be reported. ADRs will be captured retrospectively during the follow-up research interviews. This is considered a reliable source of data by the funder and manufacturer of the concentrated nasal naloxone, nyxoid who require this safety data.

As complete, as possible, narrative information on the suspected ADR and its outcome will be collected. However, we recognise that obtaining follow-up information on ADRs may be difficult within this study setting.

Participants witnessing an opioid overdose will specifically be asked about SADR and ADRs in follow-up interviews, and record answers. Fatal outcomes of overdoses are one of the endpoints of the study and will not be reported as SADRs, except if the fatal outcome is considered to have been related to THN administration or due to lack of efficacy of THN administration.

In addition, to each country's standard responsibilities on clinicians to report any adverse drug reactions to naloxone, any serious adverse drug reactions related to the concentrated naloxone nasal-spray will be reported to the manufacturer’s Drug Safety Team within 2 calendar days counting from first day of awareness (Day 0). Non-serious adverse drug reactions suspected to have a causal relationship with the concentrated naloxone nasal-spray will be reported monthly to the manufacturer’s Drug Safety Team.

### Study analysis

The rate of administration of THN by community members witnessing an opioid overdose and the frequency of deaths in the 24 h (or later if information is available) after administration of naloxone will be estimated as proportions. The study data will be stratified by participant groups as follows: 1) Patients in treatment for opioid use disorder (OUD), 2) Participants who use opioids but are not currently in treatment, 3) Friends and family members, 4) Staff working with individuals with OUD. Effective administration rates of THN by community members will be estimated as proportions. The outcomes will also be estimated for each THN formulation (including the multiple intranasal and injectable formulations that will be captured in this study).

All secondary and exploratory endpoints will be estimated as proportions. Demographic and clinical characteristic data for study participants will be reported using summary statistics for continuous variables (means and standard deviations or medians and interquartile ranges) or frequencies and percentages for categorical variables, as appropriate.

Descriptive data will be reported as numeric counts and percentages with the denominator for reporting percentages appropriate to the specific question.

The extent of missing data at each quantitative study inquiry stage will be tabulated appropriately.

The key population under investigation will be those included in the witnessed overdose cohort (~600). It is anticipated that this will only have missing item level data, as by being in the witnessed overdose cohort, they will be followed up. We do not anticipate any additional analyses in those lost to follow up between those initially enrolled (~6,000) and those included in the witnessed overdose cohort primary population (n ~ 600). We are monitoring the event rate within those initially enrolled as it could be the case, that we could stop enrolment sooner than anticipated, if the event rate is considerably higher than initially estimated.

Planned subgroup analysis will include the following: type of participant (e.g., participant witnessed an opioid overdose event, or experienced an opioid overdose event), age of participant, sex of participant, THN formulation, and carrier of THN versus non-carrier.

This study is purely descriptive in nature. No inferential statistics are planned, but, where appropriate, 95% confidence intervals will be calculated for estimates of means and proportions. The data will be collated within a REDCap database and analysed using Stata.

#### Qualitative data analysis

All qualitative interviews of Sub-study B will be transcribed verbatim, and analyses will follow the principles of Iterative Categorization. All interview transcripts will be entered into the specialist qualitative software programme MAXQDA for systematic line-by-line coding. An initial coding frame will be developed based on the topic guide (deductive codes) and this will be supplemented with inductive codes emerging from the interviews themselves. Once all the data have been coded, data extracts relating to key codes will be exported into Microsoft Word for a two-staged analytical process. First, the coded data will be reviewed descriptively to ascertain themes and patterns in the data (including naloxone understanding and training needs, carriage, use, administration, effectiveness, adverse events etc.). Second, the data will be analysed more interpretatively to explore how the various naloxone products compare; any differences between participant groups; any novel concepts and constructs emerging from the data; and how the findings link back to relevant policies, local practices, existing research evidence, and legal and regulatory frameworks.

Transcripts of qualitative interviews will be assessed by a panel of expert addiction clinicians who will examine the interview data collected (i.e., the recordings of interviews) – on which basis they will provide a scored judgement on three a priori determined clinical areas of interest, accompanied by a brief overall narrative summary. The four clinical areas of interest will be scored using a five-point Likert scale. The areas of interest will be: the accuracy of diagnosis of the probable opioid overdose crisis; the accuracy of identification of respiratory depression; the appropriateness of actions taken (including specifically of any naloxone administered as well as examination of appropriateness or otherwise of instances where naloxone was not administered); and the adequacy of the post-naloxone aftercare.

### Study sample size

Previous studies have found that approximately 10% of those supplied with THN witness an opioid overdose [19–22].

In a cohort of 600 participants who witness an opioid overdose event, we would anticipate between 6 to 63% of these events to occur when there was access (carriage/availability) to THN and for it to be used to reverse an opioid overdose in real-world practice.

#### Co-primary outcome: estimation of the true administration of THN

Therefore, using an asymptotic approach, a minimum of 553 participants would need to be interviewed to estimate the true incidence of THN administration (assumed to be 10%) with a confidence width of ±2.5% [23]. Thus, we estimate that the recruitment of 6,000 participants will lead to approximately 600 witnessed opioid overdose events (our main population for investigation) allowing for an estimation of the administration rate of THN with a precision of ±2.5%.

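### The ±2.5% precision stated for the THN administration co-primary holds with 600 events only if the true proportion is about 11% or lower, while the plan itself anticipates 6% to 63%.

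*Protocol article*

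**What the plan says.** Three statements in the protocol article bear on this point.

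- **Anticipated range.** Under *Study sample size*, for the planned 600 overdose witnesses, the authors write: "we would anticipate between 6 to 63% of these events to occur when there was access (carriage/availability) to THN". The same sentence adds that the THN is also used. This is the plan's own expectation for the quantity that the co-primary outcome measures.
- **Planning value.** Under *Co-primary outcome: estimation of the true administration of THN*, the text moves straight from that range to a large-sample calculation. Its result is that "a minimum of 553 participants would need to be interviewed to estimate the true incidence of THN administration (assumed to be 10"%). The target behind this number is a half-width of 2.5 percentage points.
- **Conclusion.** The next sentence expects 6,000 recruits to yield about 600 witnessed overdoses, and it presents that number as "allowing for an estimation of the administration rate of THN with a precision of ±2.5"%. This sentence does not repeat the 10% condition.

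The section gives no reason for choosing 10% from within 6% to 63%, and no precision for any other value. The confidence level is not stated beside the calculation, but *Study analysis* says that, where appropriate, "95% confidence intervals will be calculated for estimates of means and proportions".

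**The concern.** The width of a confidence interval for a proportion depends on p(1−p), which grows as p approaches 50%. The anticipated range runs from 6% through 50% to 63%, so most of it gives wider intervals than 10% does. A precision worked out at 10% and then stated for the study as a whole promises more than 600 events deliver over most of the values that the plan considers possible.

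The study is described as purely descriptive, with no inferential statistics planned. There is no power calculation behind it, so the precision statements are the statistical justification for its size. A reader who takes ±2.5% as a property of the design would expect a narrower co-primary estimate than the study would give at, say, 30% or 50%.

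**Working it through.** **Inputs, all from the protocol article**

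- Planning proportion p = 0.10, target half-width d = 0.025, stated minimum n = 553 (*Co-primary outcome: estimation of the true administration of THN*)
- About 600 witnessed events (same section)
- Anticipated range 6% to 63% (*Study sample size*)
- 95% confidence, z = 1.96 (*Study analysis*; stated there for estimates in general)

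**Step 1: reproduce the plan's figure.** The asymptotic (Wald) formula for one proportion is n = z² p(1−p) / d².

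n = 1.96² × 0.10 × 0.90 / 0.025² = 3.8416 × 0.09 / 0.000625 = 553.2

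This matches the stated 553 (strictly, 554 when rounded up). A finite-population correction with N = 6,000 would give 507, so none was used. The method and the 95% level are therefore identified.

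**Step 2: half-width with 600 events.** Half-width = 1.96 × √(p(1−p)/600). The last column is 1.96² p(1−p)/0.025², rounded up.

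| True proportion | Half-width with 600 events (points) | Events needed for ±2.5 |
|---|---|---|
| 6% | ±1.90 | 347 |
| 10% | ±2.40 | 554 |
| 20% | ±3.20 | 984 |
| 30% | ±3.67 | 1,291 |
| 50% | ±4.00 | 1,537 |
| 63% | ±3.86 | 1,433 |

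**Step 3: where ±2.5 stops holding.** Set 1.96 × √(p(1−p)/600) = 0.025:

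p(1−p) = 600 × (0.025/1.96)² = 0.0976

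p = (1 − √(1 − 4 × 0.0976)) / 2 = 0.1096

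So ±2.5 is met from 6% up to 10.96% and missed from there to 63%. As a share of the anticipated span, the part that misses is (63 − 10.96) / (63 − 6) = 52.04 / 57 = 91%.

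**Step 4: is this an artefact of the interval method?** No. Wilson half-widths with 600 events are 2.41 at 10%, 3.20 at 20%, 3.99 at 50% and 3.85 at 63%, all within 0.02 points of the Wald values.

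**The case against.** The strongest reply is that nothing is miscalculated and the condition is stated. The 10% stands in the sentence that gives 553, the next sentence carries the same calculation forward, and 10% lies inside the 6% to 63% range, so the two statements do not formally contradict each other. Every precision figure based on one planning value holds only near that value. This is right as far as it goes. What remains is that the value chosen is close to the end of the range that flatters precision, that no reason is given, and that the closing sentence states ±2.5% for the study without a condition.

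A second reply concerns consequence. No test, margin or power figure depends on ±2.5%, and the intervals reported at the end will show what was achieved. An estimate of 50% with limits of 46% and 54% still answers the co-primary question; in relative terms ±4.0 on 50% is 8%, against 24% for ±2.4 on 10%. This stands, and it limits how serious the point is.

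Four stronger readings are tempting, and the documents do not support them.

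- **The 10% was borrowed from another quantity.** The section also reports that "approximately 10% of those supplied with THN witness an opioid overdose", and a reader might infer that this figure was carried over. Nothing in the article shows it, and the justification may stand in the full protocol, which is not at hand.
- **There is a 91% chance of missing ±2.5.** The article gives a span and not a distribution. The 91% describes how much of the span fails, not how likely failure is.
- **The study is too small.** The article sets no requirement that ±4.0 would fail, beyond the ±2.5% itself.
- **The nasal-spray subgroup falls short of a promised precision.** The article claims no precision for the roughly 300 nasal-spray witnesses, so there is no promise to contradict.

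**Conclusion.** The point holds. The ±2.5% follows correctly from 10%, but as a statement of what about 600 witnessed overdoses will deliver it is true only if the administration proportion is about 11% or lower. Over the rest of the plan's own 6% to 63% range the half-width is larger, up to ±4.0 points at 50%.

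The size is moderate: at worst 1.5 points wider than stated (4.0 − 2.5), in a descriptive study that will report its achieved intervals. The statement should be corrected, but it does not call the design into question.

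The figures assume 95% two-sided intervals, 600 interviewed witnesses contributing one event each, independence between events, and that the 6% to 63% range refers to the administration proportion, as its wording on access and use indicates. Clustering by site or country, if present, would usually widen the intervals further; the article gives no figure from which to quantify that.

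**What to change.** In *Co-primary outcome: estimation of the true administration of THN*, replace the closing ±2.5% claim with wording such as:

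> 600 interviewed witnesses estimate the administration proportion with a 95% half-width of ±1.9 to ±4.0 percentage points over the anticipated 6–63% range (±2.4 at 10%; worst case ±4.0 at 50%).

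The 553 can stay as the number needed at 10%, provided that it is labelled as such.

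The cost is a sentence of rewording and a stated precision that looks less favourable. Recruitment targets, data collection and analysis do not change. Holding ±2.5 points across the whole range would instead need up to 1,537 witnessed events, and nothing in the article suggests that this is necessary.

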#### Co-primary outcome: estimation of mortality rate

Assuming a morality rate of 1.4% [20, 22], using a sample size of 600 will allow the estimation of the 95%CI within a width of ±1.5%. We anticipate approximately 8 deaths from the 600 witnessed overdoses reported by participants.

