### Objectives and outcome

#### Main study objectives

There are two co-primary objectives:To determine the frequency of deaths in the 24 h (or later if information is available) subsequent to administration of naloxone by community members, to reverse an opioid overdose in real world settings.To determine the proportion of naloxone administration with the intention of reversing an opioid overdose by community members provided with THN who witness an opioid overdose.

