#### Main study outcomes

Co-primary outcomes (of witnessed overdose cohort) include:

Among community members provided with a supply of THN and witnessing an opioid overdose, a) the proportion administering THN to reverse an opioid overdose, and the frequency of deaths within 24-h (or later if information is available) after administration of THN. Overdose events eligible for inclusion in the primary outcome analysis are opioid overdoses witnessed by the participant during the six-month period after study enrolment.

Secondary outcomes include:

Of the Total cohortPercentage of participants who report carrying THN (on day of interview)Percentage of participants who witness an opioid overdose over 6-month periodPercentage of participants, who are at a risk of experiencing an opioid overdose themselves, who report experiencing an opioid overdose (fatal or non-fatal)”

Of the Witnessed overdose cohort:Percentage of participants who are carrying THNPercentage of participants who report there was THN presentPercentage of participants who state there was THN present, and administer THNPercentage of participants who administer THN and report that respiratory depression occurred in the person they resuscitated within one hour of THN administrationPercentage of participants who report administering a second dose of THN to a person experiencing an opioid overdose, within 1-h post administration of first dose of THNPercentage of participants who report that withdrawal symptoms and/ or anger, rage or violence occurred in person they resuscitated with THN. Frequency of each symptom witnessed (at most recent overdose witnessed)Percentage of participants who report that the person receiving naloxone has survived at 2 h post administration of naloxone, OR at arrival of ambulance/medical assistance, if this occurs before 2 h have passed since the opioid overdosePercentage of participants who report fatal outcomes within 2 h of the identification of opioid overdose, or at the arrival of an ambulance/medical assistance, where THN was administered and where THN was not administeredPercentage of participants who correctly diagnose opioid overdose crisis (assessed through multiple response questions)

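### The mortality co-primary is defined among overdoses where naloxone was given, but its expected deaths and precision are worked out on all 600 witnessed overdoses

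*Protocol article*

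**What the plan says.** The outcome is tied to administration in three places in the protocol article. Main study objectives refers to deaths "subsequent to administration of naloxone by community members, to reverse an opioid overdose in real world settings". Main study outcomes gives "the frequency of deaths within 24-h (or later if information is available) after administration of THN". Study analysis says that the frequency of deaths "after administration of naloxone will be estimated as proportions".

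The sizing uses another population. Under Co-primary outcome: estimation of mortality rate, a mortality of 1.4% is assumed and the text states that "using a sample size of 600 will allow the estimation of the 95%CI within a width of ±1.5"%. It continues: "We anticipate approximately 8 deaths from the 600 witnessed overdoses reported by participants".

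The neighbouring paragraphs say how often THN is expected to be given. The opening of Study sample size anticipates that, of 600 witnessed events, 6 to 63% will be ones where THN was accessible and used. The paragraph on the other co-primary sets the sample size "to estimate the true incidence of THN administration (assumed to be 10"%). Nowhere is the 600 reduced to administered cases for the mortality estimate.

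**The concern.** A proportion of deaths after administration has administrations as its natural denominator. Using 600 amounts to assuming that THN is given at every witnessed overdose, while the paragraph just before assumes that it is given at one in ten. The two co-primary calculations then rest on incompatible assumptions about the same 600 events.

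What is at stake is how much the study can say about mortality after community use of naloxone. A reader of the sample size section expects about 8 deaths and an interval no wider than ±1.5 points. Under the protocol's own planning value, the defined outcome may yield one death or none, and an interval compatible with mortality several times the assumed 1.4%.

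**Working it through.** **Inputs (all from the protocol article).** 600 witnessed overdoses and 1.4% mortality (mortality sizing paragraph); 10% administration (administration sizing paragraph); 6 to 63% access and use (Study sample size); 95% two-sided intervals (Study analysis gives 95% as the level).

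**1. Reproduce the stated figures.**
- Administration co-primary: n = 1.96² × 0.10 × 0.90 / 0.025² = 553.2. This matches the stated 553, so the asymptotic (Wald) formula is the one used there.
- Deaths: 600 × 0.014 = 8.4. This matches the stated 8, and shows that all 600 are the denominator.
- Precision at n = 600: 1.96 × √(0.014 × 0.986 / 600) = 0.94 points. Wilson gives 0.99. The exact (Clopper-Pearson) interval for 8/600 is 0.58 to 2.61%, a half-width of (2.61 − 0.58)/2 ≈ 1.0. All lie within ±1.5.

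**2. Move to the defined denominator.** Administered cases n = 600 × administration rate; expected deaths = 0.014 × n; Wald half-width = 1.96 × √(0.014 × 0.986 / n); chance of no death = 0.986ⁿ. This step takes 1.4% as the mortality among administered cases.

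| Administration rate | n | Expected deaths | Wald half-width (points) | Chance of no death |
|---|---|---|---|---|
| 6% | 36 | 0.50 | ±3.84 | 60% |
| 10% (planning value) | 60 | 0.84 | ±2.97 | 43% |
| 30% | 180 | 2.52 | ±1.72 | 8% |
| 40% | 240 | 3.36 | ±1.49 | 3% |
| 63% | 378 | 5.29 | ±1.18 | 0.5% |

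**3. Exact intervals, because events are few.**
- 1/60: 0.04 to 8.94%
- 5/378: 0.43 to 3.06%, half-width (3.06 − 0.43)/2 ≈ 1.3 points

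**4. When is ±1.5 met?**
- Wald: n = 1.96² × 0.014 × 0.986 / 0.015² = 235.7, so about 236 administrations, and 236/600 = 39%.
- Wilson half-width: 286 administrations (286/600 = 48%).
- Clopper-Pearson half-width: 313 administrations (313/600 = 52%).
- At 10% administration, 236 administrations would need about 236/0.10 = 2,360 witnessed overdoses.

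**5. When are 8 deaths expected?** 8/0.014 = 571 administrations, and 571/600 = 95%. The top of the anticipated range is 63%.

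**The case against.** The strongest counter-argument is that the denominator is open to reading. Main study outcomes lists both co-primaries under the witnessed overdose cohort, and Study analysis calls the roughly 600 the key population. The 1.4% comes from cited studies that are not available here. If it describes all witnessed overdoses, 8 in 600 is sound arithmetic and the fault is one of labelling.

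This stands in part. On that reading the figure sizes mortality among all witnessed overdoses, which is not the outcome in the objectives, the outcomes or the analysis. Keeping 600 as denominator while counting only deaths after administration does not rescue it either. At 10% administration and 1.4% mortality among those cases, the numerator is 0.84, and 0.84/600 = 0.14%.

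A second objection is that the ±1.5 claim is a bound and does not fail everywhere. That is right: by Wald it holds from about 39% administration upwards, and at 63% the exact half-width is also inside it. The claim fails over the lower part of the range, which includes the planning value.

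Third, the study is descriptive. No test depends on these figures, and the 553 needed for the other co-primary already supports 600. So the point does not undermine the choice of 600; it concerns what that number delivers for mortality.

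**Conclusion.** The expected deaths and the precision stated for the mortality co-primary do not belong to the outcome as defined. At the protocol's 10% administration rate, expect 0.84 deaths where 8 are stated, and a Wald half-width of ±3.0 points, about twice the ±1.5 bound. Over 6 to 63% the figures are 0.5 to 5.3 deaths and ±3.8 to ±1.2 points. This rests on 1.4% applying to administered cases, which the text does not say, and on 600 witnessed overdoses being reached.

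Four stronger readings are tempting but not supported:
- **That ±1.5 is miscalculated at n = 600.** The text says within that width, and ±0.94 satisfies it. The bound is loose but true for that denominator.
- **That the interval runs below zero (1.4 − 1.5).** This treats the bound as the achieved width. The Wald interval at 600 is 1.4 ± 0.94, or 0.46 to 2.34%.
- **That the early-stop remark makes it worse.** The text says only that "we could stop enrolment sooner than anticipated, if the event rate is considerably higher than initially estimated". This is a possibility with no fixed rule, and stopping once about 600 witnessed events are in hand would leave the planned number of administrations unchanged.
- **That the nasal-spray half contradicts a stated precision.** None is stated for it, and splitting the administrations would require assuming equal use across formulations, which the protocol does not say.

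**What to change.** In the mortality sizing paragraph:

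1. State the denominator as witnessed overdoses at which THN was administered, and use the same wording in the objectives, outcomes and analysis.
2. Say which population the 1.4% describes.
3. Replace the single figures by expected deaths and precision for 36 to 378 administrations, with the 10% planning value (60) shown. Use exact or Wilson intervals, since the expected number of deaths is 5 or fewer over nearly all of the range.
4. Keep 8 in 600 (exact 95% interval 0.58 to 2.61%) only if it is labelled as mortality among all witnessed overdoses.

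The change is to wording and needs no new data or procedures. Its cost is a less favourable stated precision for this co-primary.
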